## Abstract

**Introduction:**

Undernutrition leading to unplanned weight loss is common in older age and has been linked to increased dementia risk in later life. Weight loss can precede dementia by a decade or more, providing a unique opportunity for early intervention to correct undernutrition and potentially prevent or delay cognitive impairment. The combined effects of diet and exercise on undernutrition have not yet been evaluated. The objective of this trial is to determine the effect of a protein-enriched Mediterranean diet, with and without exercise, on nutritional status and cognitive performance in older adults at risk of undernutrition and cognitive decline.

**Methods:**

One hundred and five participants aged 60 years and over at risk of undernutrition and with subjective cognitive decline will be recruited to participate in a 6-month, single-blind, parallel-group randomised controlled trial. Participants will be block randomised into one of three groups: group 1—PROMED-EX (diet+exercise), group 2—PROMED (diet only) and group 3—standard care (control). The primary outcome is nutritional status measured using the Mini Nutritional Assessment. Secondary outcomes include cognitive function, nutritional intake, body composition, physical function and quality of life. Mechanistic pathways for potential diet and exercise-induced change in nutritional status and cognition will be explored by measuring inflammatory, metabolic, nutritional and metabolomic biomarkers.

**Ethics and dissemination:**

The study is approved by the UK Office for Research Ethics Committee (ref: 21/NW/0215). Written informed consent will be obtained from participants prior to recruitment. Research results will be disseminated to the public via meetings and media and the scientific community through conference presentations and publication in academic journals.

**Trial registration number:**

ClinicalTrials.gov Registry (NCT05166564).

STRENGTHS AND LIMITATIONS OF THIS STUDYThis is the first randomised controlled trial designed to evaluate the effect of an optimised protein-enriched Mediterranean diet, with and without exercise, on nutritional status and cognitive performance in a high-risk population.The integration of state-of-the-art metabolomics, metabolic, inflammatory and nutritional biomarkers will help elucidate biological mechanisms underlying how diet can influence nutrition status and cognition and how exercise can interact with nutrition to modify these processes.A patient and public involvement group will contribute at all stages of the PROMED-EX trial to optimise the research design and dissemination strategy of the research findings.The nature of the ‘real-world’ pragmatic study design means that it is not possible to blind participants to treatment allocation, possibly leading to performance bias.Data will be analysed by a blinded member of the study team to minimise detection bias.

## Introduction

Undernutrition, defined as insufficient food and/or nutrient intake that results in altered body composition and unplanned weight loss,^1^ is common in older age and affects >1.3 million older adults in the UK.^2^ Individuals with cognitive impairment are particularly vulnerable to undernutrition and its many adverse consequences. Undernourished people with dementia experience more rapid decline in cognitive and physical functions, increased neuropsychiatric symptoms, and greater risk of hospitalisation and mortality, than those with adequate nutritional status.^3 4^ Being undernourished has also emerged as a potentially modifiable risk factor for dementia.^5^ In prospective studies, weight loss has been associated with increased dementia risk,^6^ and precedes the onset of dementia by a decade or more,^7 8^ making it an intervention target that should be prioritised.

Causes of undernutrition are increased nutrient requirements, inadequate dietary intake and reduced nutrient bioavailability,^9^ but the exact mechanisms of undernutrition in dementia are not clear. It is possible that weight loss may be both a consequence and cause of neurodegeneration and dementia. Loss of muscle and weight in older adults has been linked to accelerated decline in brain structures,^10–12^ even after exclusion of cognitive impairment,^12^ suggesting a pathophysiological role of undernutrition in dementia. In contrast, weight loss could be an early marker of dementia development. Pathological changes in the brain are present 10–15 years prior to the clinical symptoms of cognitive impairment and induce inflammatory^13^ and physiological changes beyond normal ageing that can have a negative impact on nutrition and body weight. Dementia pathology affects brain regions such as the hypothalamus which is important for appetite regulation and eating behaviour.^14^ This may explain alterations of leptin and ghrelin metabolic signals that are observed in early disease.^15^ Early brain changes can also affect chemosensory perception including taste and olfactory function,^16^ as well as satiety regulation, protein and lipid synthesis,^17^ and food preferences. Disease progression and worsening cognitive impairment can cause forgetfulness to eat, dysphagia,^18^ sleep disturbance^19^ and social withdrawal,^20^ which can all have adverse effects on food intake.^21^

To date, most studies have focused on the impact of diet on physical function,^22^ with limited number of interventions targeting undernutrition for cognitive benefit. Short-term treatment of undernutrition has been shown to improve both nutritional status and cognitive performance.^23–25^ However, small sample sizes as well as differences in residential status of study populations and nutritional interventions (dietetic counselling,^23^ oral supplementation,^24 25^ meal provision^25^), and cognitive outcomes make it difficult to know whether addressing undernutrition could protect against cognitive decline. Hence, trials are warranted to test the efficacy of intervention for undernutrition in populations at increased risk of cognitive decline but not yet cognitively impaired and may benefit from early intervention.

The Mediterranean diet (MedDiet) is a nutrient-dense dietary pattern with proven anti-inflammatory benefits^26^ and may offer protection against cognitive decline during ageing. Observational data have reported links between the MedDiet and favourable changes in brain structures and functions,^27^ slower rate of cognitive decline^28 29^ and decreased dementia risk,^30 31^ which appear to be attributable to the combined effect of different foods rather than the action of a single food or nutrient.^32^ Furthermore, the MedDiet is associated with nutritional adequacy and lower risk of undernutrition and micronutrient deficiency.^33^ Adequate protein (1.0–1.2/kg body weight/day)^34^ and energy intake^35^ are critical for preventing muscle loss^36^ and undernutrition in older adults.^37^ However, emerging data suggest that a high-quality dietary pattern is also important,^38^ lending support to a ‘whole diet’ approach for preventing muscle loss and functional decline during ageing.

Physical exercise has positive effects on cognition,^39^ especially in domains of executive function and processing speed,^40^ by increasing neurogenesis and upregulating neurotrophic factors.^41^ However, it is not known how diet and exercise interact for neuroprotection. Multidomain interventions that include both a healthy diet and exercise appear to elicit stronger positive results for cognitive performance than each intervention in isolation.^42^ Furthermore, exercise can stimulate protein synthesis^43^ and enhance muscle mass and functional performance in older adults,^44^ making it an attractive target for preventing undernutrition. An optimal protein MedDiet may induce additive effects on nutritional status and cognition when combined with exercise, but this has not yet been evaluated.

The PROtein enriched MEDiterranean Diet and EXercise (PROMED-EX) randomised controlled trial (RCT) aims to determine the effects of a protein-enriched MedDiet, with and without exercise, in comparison with standard care, on nutritional status in adults at risk of undernutrition and cognitive decline. PROMED-EX is part of the European ‘PROMED-COG’ Project, funded under the Horizon Joint Programming Initiative ‘A Healthy Diet for a Healthy Life’ to establish evidence for the balance between diet and physical activity for preventing undernutrition and promoting healthy neurocognitive ageing.^45^

## Methods and analysis

PROMED-EX is a 6-month, single-blind, parallel-group RCT aiming to recruit 105 eligible adults residing in Northern Ireland (NI), aged 60+ years and at risk of both undernutrition and cognitive decline. The protocol has been written in accordance with the Standard Protocol Items: Recommendations for Interventional Trials guidelines,^46^ and a summary is reported using the checklist (online supplemental appendix 1). An independent Trial Steering Committee (TSC) has been established (online supplemental appendix 2) to oversee the conduct of the study.

10.1136/bmjopen-2022-070689.supp1Supplementary data

10.1136/bmjopen-2022-070689.supp2Supplementary data

### Patient and public involvement

A patient and public involvement (PPI) group (n=8) comprising older adults residing in NI with lived experience of subjective cognitive decline (SCD) and/or poor nutritional status were recruited for PROMED-EX. PPI members have contributed to the intervention design and co-development of materials, including lay summary, participant information sheet and consent form, advertisement materials and written educational resources for the interventions. Besides the trial design, two PPI members sit on the TSC and will provide input to future stages including implementation, analysis and dissemination.

### Study design

Study participants will be randomised into one of three groups: group 1—PROMED-EX: protein-enriched MedDiet and exercise intervention (n=35); group 2—PROMED: protein-enriched MedDiet intervention (n=35); or group 3—control: standard care healthy eating diet sheet (n=35) as shown in figure 1. Participants will be informed of their allocated group after baseline data have been collected. Those randomised to the PROMED-EX and PROMED interventions will receive active support to adopt the behavioural targets in the first 3 months, after which time they will continue with self-directed maintenance of the newly adopted behaviours for a further 3 months.

**Figure 1 F1:**
[figure not shown]
Overview of PROMED-EX Study design. PROMED-EX, PROtein enriched MEDiterranean Diet and EXercise.

### Sample size

As no prior studies have evaluated the effects of whole diet and exercise on nutritional status and cognition, the sample size calculation is based on an SD of the change in Mini Nutritional Assessment (MNA) score of 4 points over a similar period from the control group of a previous nutrition intervention.^47^ A total of 28 completing in each intervention and control group would provide over 80% power to detect a difference in the three means, based on a statistically significant analysis of variance (ANOVA) result at the 5% level, hypothesising a true increase in MNA of 3 or more in both intervention groups, but not the control group. Loss to follow-up is estimated from our prior experience of conducting lifestyle trials in older adults^48–50^ where attrition ranges from 6%^50^ to 30%.^49^ Considering, FINGER^42^ evaluated an intensive multidomain lifestyle intervention among older adults at increased dementia risk and reported 12% withdrawal over 2 years. We anticipate dropout at 20% and therefore have added 20% to the sample size to account for non-compliance, dropout or discontinuation.

### Recruitment and eligibility of study participants

Multiple recruitment strategies will be employed including paid Facebook advertisements, other media (eg, newspaper, radio and television), and identification of potentially eligible participants from community networks, primary care sectors and health and social care trusts in NI. Those interested in participating will be provided with an information sheet detailing the study protocol, followed by a phone call to discuss study procedures.

Potentially eligible participants will be screened by telephone/video to last around 45 min. Individuals will be eligible to enrol if they are community dwelling, aged ≥60 years, at risk of undernutrition defined by an MNA-Short Form score of 8–11^51^ and have a positive screen for SCD.^52^ The screening assessment includes the Telephone Cognitive Screen or Mini Mental State Examination (MMSE) to exclude participants with cognitive impairment and a health and medical history questionnaire to determine if the participant has any medical conditions that compromise their ability to take part. This includes if they receive nutritional support, have a diagnosis of mild cognitive impairment or dementia, or dietary restrictions as shown in table 1.

**Table 1 T1:** PROMED-EX trial eligibility criteria

Inclusion criteria	Exclusion criteria
Age ≥60 years Community dwelling Mini Nutritional Assessment-Short Form score 8–11, indicating increased risk of undernutrition^51^ Positive screen for subjective cognitive decline^52^ defined as a ‘yes’ response to the question: ‘During the past 12 months, have you experienced confusion or slight memory loss that is happening more often or is getting worse?’ Ability to provide informed consent	Cognitive impairment: Telephone Cognitive Screen ≤21 or Mini Mental State Examination ≤24 or clinical diagnosis of mild cognitive impairment or dementia In receipt of prescribed oral or artificial nutritional support Dietary restrictions/allergies to PROMED foods (eg, nuts) or taking high-dose nutritional supplements (eg, vitamin E) that limit the ability to take part in the study Living in long-term care facilities Self-reported: Dysphagia Chronic kidney disease Diabetes complications or HbA1c >8% Significant medical comorbidities that may alter cognitive test performance, for example, stroke, brain injury Inability to complete cognitive testing due to language or visual impairment

PROMED-EX, PROtein enriched MEDiterranean Diet and EXercise.

### Randomisation, blinding and allocation

A study statistician independent of recruitment, intervention delivery and data collection will perform block randomisation using a computer-generated random number sequence in blocks of size 6 (using command RALLOC in STATA V.16, StataCorp, College Station, USA). Allocations will be prepared in sealed opaque envelopes by an independent study administrator and will not be revealed to participants until completion of baseline data collection. It will not be possible to blind the participant nor study researchers involved in intervention delivery to the allocated intervention group; however, data collection and analysis will be carried out by investigators blinded to treatment allocation.

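### A single fixed, published block size of 6 with unblinded delivery researchers lets anyone who follows the sequence deduce up to about a fifth of allocations

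*Protocol article*

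**What the plan says.** The article describes a "6-month, single-blind, parallel-group RCT aiming to recruit 105 eligible adults" (Methods and analysis), with three arms of 35 each (Study design). Under Randomisation, blinding and allocation, a statistician who is independent of recruitment, delivery and data collection produces the list "using a computer-generated random number sequence in blocks of size 6". No other block size, variation in size or stratification is mentioned. An independent administrator prepares sealed opaque envelopes, and participants learn their group only after baseline data are complete.

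On blinding, the same section says "It will not be possible to blind the participant nor study researchers involved in intervention delivery to the allocated intervention group", and then that "data collection and analysis will be carried out by investigators blinded to treatment allocation".

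Recruitment and eligibility of study participants describes an explanatory telephone call and a screening contact of about 45 minutes. It does not say which staff make them.

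**The concern.** With a constant block size, the end of each block follows from its beginning. The delivery researchers see the allocations as they occur, because the arms differ visibly: food deliveries and weekly calls in both diet arms, an exercise prescription in one of them, and a diet sheet only in the control arm. The block size is in a public article. The envelopes protect against reading the next assignment, not against working it out.

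If someone with this knowledge also screens or enrols, the expected arm could affect who is encouraged to join, how a judgement-based exclusion is applied, or when a participant is booked. The analysis leans on randomisation here: Data management and statistical analysis plan says that no covariates are planned because randomisation will make the groups similar, and the primary model adjusts only for the baseline score. Selection on traits that the baseline score does not capture would go uncorrected.

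**Working it through.** **Inputs.** Block size 6 (Randomisation, blinding and allocation); three arms (abstract, Methods); 35 per arm, so two places per arm in each block (Study design); 105 in total (Methods and analysis). The article gives no figure for predictability. Its sample size is consistent: 28 / 0.8 = 35 per arm, and 3 × 35 = 105.

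**Assumptions.** There is one list, and the observer knows the block size, the block boundaries and every earlier allocation in the current block.

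**Allocations fully determined.** A block has 6! / (2! 2! 2!) = 90 equally likely orders.
- Places 1 to 4 are never certain.
- Place 5 is certain only if the last two places belong to the same arm, with probability 1/5.
- Place 6 is always certain.
- Expected number per block: 1/5 + 1 = 1.2, and 1.2 / 6 = 20%.

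For 105 participants: 105 = 17 × 6 + 3. The last three places open a new block, and none of them is certain. So 17 × 1.2 = 20.4, and 20.4 / 105 = 19.4%.

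**Active versus control certain (full block).** The two control places are equally likely to be any of 15 pairs.
- Expected places after the second control, all certain to be active: 4/3 = 1.333.
- Expected places where only controls remain: 1/3 (place 6 is control) + 1/15 (places 5 and 6 are both control) = 0.4.
- Total: 1.733 / 6 = 28.9%.

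**Best guess of the arm.** Always name the arm with the most places left.

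| Place | 1 | 2 | 3 | 4 | 5 | 6 |
|---|---|---|---|---|---|---|
| P(correct) | 1/3 | 2/5 | 1/2 | 8/15 | 3/5 | 1 |

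The sum is 3.367, and 3.367 / 6 = 56.1%, against 33.3% by chance.

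**Effect of varying the block size.** This was simulated with 300 sequences of 105, sizes drawn with equal probability, and an observer who knows the set of sizes but not their order. The sets are illustrative.

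| Block sizes | Allocations certain |
|---|---|
| 6 only | 19.4% (agrees with the exact figure) |
| 3 and 6 | about 9% |
| 6 and 9 | about 5% |
| 3, 6 and 9 | about 4% |

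**The case against.** The strongest reply is that the article does not contain the whole route to bias. It says that delivery researchers are unblinded, not that they screen or enrol. Data collectors are blinded, and both sequence generation and envelope preparation are in independent hands. A condensed article may leave the enrolling role to the full protocol, so silence on it is not evidence of overlap. If staff who know no past allocations do the enrolling, the risk largely disappears. Allocation also follows screening, consent and baseline assessment, so a screener would have to anticipate the order in which people reach randomisation. Fixed blocks are a recognised choice.

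All of this stands, and it makes the figures conditional upper bounds. It does not remove the point: the constant block size is a stated parameter, booking times can be steered, and only the statistician is said to be independent of recruitment.

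A reader might infer two further things that the article does not support.
- **That bias would act through motivation, which the article already names as a confounder.** The Discussion's remark concerns completers who become more motivated because only the active arms receive weekly contact. That arises after randomisation and is not selection at entry.
- **That 105 not being a multiple of 6 threatens the sample size.** The last three places fall one per arm with probability 36/90 = 40%; otherwise the split is 36/35/34. On the article's assumptions (means 3, 3 and 0, SD 4, 5% ANOVA), with the control arm the smallest, power is 89.8% instead of 90.2% with everyone analysed. At 29/28/27 completers it is 81.3% instead of 82.0%. The loss is under one percentage point, and varying the block size would not guarantee 35 per arm either.

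**Conclusion.** The point holds as an inexpensive improvement to a stated design choice. It is not an error or a contradiction in the plan. With fixed blocks of 6 and three arms, at most 20.4 of 105 allocations (19.4%) are deducible. In a full block, about 29% are certain as active versus control, and the best guess is right 56% of the time against 33% by chance.

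These figures need an observer who knows the block size and all earlier allocations in the block. Selection bias needs, in addition, that this person, or someone they inform, can influence who is enrolled or when. The article leaves that open. The actual effect may be well below the bound or nil, and no bias in the Mini Nutritional Assessment score can be estimated from what is given.

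It would go too far to say that the design makes one allocation in five known in advance, or that the analysis could repair none of the resulting bias. Baseline adjustment deals with selection acting through the baseline score, though not through unmeasured traits.

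**What to change.** For any allocations still to be made, regenerate the list with randomly varying block sizes that are multiples of 3, for example 3, 6 and 9. Keep the new sizes within the statistician's office until recruitment closes. State that those who screen and enrol do not know past allocations, and arrange the work so that this is true. If recruitment has finished, report who enrolled participants and what they knew of earlier allocations.

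The cost is a new list and a new set of envelopes. The possible imbalance when recruitment stops is slightly larger: a block of 9 cut short can leave one arm three ahead of another, against two for a block of 6. The size of 6 is already public, and the article does not show how many allocations remain, so the gain is limited to those still to come.

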### Interventions

#### Group 1: PROMED-EX

##### Protein-enriched MedDiet intervention

The PROMED-EX trial will be overseen by a registered dietitian ([name]). Participants will meet a trained researcher, with a background in nutrition and exercise within 1 week following randomisation to receive personalised dietary counselling based on their baseline anthropometry, MNA score and PROMED diet score (online supplemental appendix 3). This session will last up to 60 min where education will be provided on adequate nutritional status, avoiding weight loss and encouraging regular meal pattern. Participants will be encouraged to set dietary goals to adopt PROMED diet behaviours (shown in Box 1) to achieve overall intervention targets: (1) increased protein intake up to 1.5 g/kg current body weight,^37^ (2) increased MNA score by ≥2 points and (3) increased PROMED diet score by ≥2 points. Daily energy requirements will be calculated at 30 kcal/kg of body weight with a supplement of 400–600 kcal only if weight gain is indicated.^53^

10.1136/bmjopen-2022-070689.supp3Supplementary data

Box 1PROMED diet behaviours
